## **6.0 Statistical Considerations**

Patients will be treated based on an optimal plan derived for each patient. We plan to enroll a maximum of 35 patients. We expect to encounter 2 lesions requiring treatment per patient. The primary endpoint is lesion failure within the first 6 months based on imaging assessments for each lesion. The evaluable study population will consist of patients who reach the 6-month evaluation point for local control. We will assume that failure of a lesion is independent of failure for all other lesions. However, an exploratory analysis will be conducted to assess this assumption as evidence suggesting within patient correlation is not available in the published literature.

Patients' lesions will be followed for failure starting on day 1 of radiation treatment in 3-month intervals (+/-2 months) for up to 1-year. Patients unable to complete at least 80% of their prescribed dose will be replaced.

We plan to evaluate efficacy at the level of the lesion. However, this study will monitor futility attributable to patient benefit at the patient-level using local control in consort with the assessment criteria for lesions.

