### **4.0 Research Plan and Methods**

The study utilizes a two-stage design with an inherent interim analysis after the first stage to stop the study early for futility. In the first stage of the study, the first 20 evaluable (defined as patients who complete the 6 month follow up) patients (See study design below) will be analyzed prior to making a decision to continue to the second stage of the study. Study data will be collected and managed using REDCap (Research Electronic Data Capture) electronic data capture tools hosted at MD Anderson. REDCap ([www.project-redcap.org](http://www.project-redcap.org)) is a secure, web-based application with controlled access designed to support data capture for research studies, providing: 1) an intuitive interface for validated data entry; 2) audit trails for tracking data manipulation and export procedures; 3) automated export procedures for seamless downloads to common statistical packages; and 4) procedures for importing data from external sources. In the case of multi-center studies REDCap uses Data Access Groups (DAGs) to ensure that personnel at each institution are blinded to the data from other institutions. REDCap (<https://redcap.mdanderson.org>) is hosted on a secure server by MD Anderson Cancer Center's Department of Research Information Systems & Technology Services. REDCap has undergone a

Governance Risk & Compliance Assessment (May 2014) by MD Anderson's Information Security Office and found to be compliant with HIPAA, Texas Administrative Codes 202-203, University of Texas Policy 165, federal regulations outlined in 21CFR Part 11, and UTMDACC Institutional Policy #ADM0335.

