## 6.2 Futility Monitoring

Futility monitoring will be conducted to stop the trial early if there is no observed benefit at the patient-level. The patient-level LC rate at 6-months will be used to monitor the trial for futility. We will estimate the LC rate at 6 months. The Green-Dahlberg two-stage design (<http://www.swogstat.org/stat/public/Help/twostage.html>) will be used to terminate the trial early for futility. The null hypothesis is that the 6-month LC rate is  $\leq 55\%$  and is not as effective as previously believed, thus requiring early termination of the trial for futility. The alternative hypothesis is that the LC rate at 6-months is clinically advantageous as demonstrated by a 6-month LC rate  $\geq 75\%$ . Hypothesis testing will be conducted using a one-sided test,  $\alpha = 0.05$ , and Type II error of 0.20. The probability of stopping at the end of Stage 1 is 0.409 if the null hypothesis is true, and the probability of stopping at the end of Stage 1 is 0.014 if the alternative hypothesis is true.

We will enroll a total of 35 evaluable patients. Initially, 20 patients will be enrolled in the first Stage of the study and evaluated for response at 6-months from day 1 of radiation treatment. If there are at least 11 patients among the first 20 who achieve LC at 6-months, then an additional 15 patients will be enrolled and evaluated. Note that the 20th patient in the first Stage must be evaluated for response prior to continuing to the second stage when less than 11 patients have experienced LC at 6-months. Finally, if there are at least 25 patients achieving LC at 6-months among all 35 patients, then we will reject H0. The statistical assessments will be used to design and appropriately power a Phase III study if warranted based on the outcomes we observe in this Phase II study.

Figure 1 Study Schema

[figure not shown]

Table 1. Description of the 2 Stage Design

|                                                                                 |                            |  |
|---------------------------------------------------------------------------------|----------------------------|--|
|                                                                                 | Study Cohort               |  |
| Null Hypothesis                                                                 | LC at 6 months $\leq 55\%$ |  |
| Alternative Hypothesis                                                          | LC at 6 months $\geq 75\%$ |  |

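### The protocol caps enrolment at 35 patients yet needs 35 patients evaluable at 6 months, and the two figures agree only if no enrolled patient is lost or replaced

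*Protocol*

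**What the plan says.** Section 6.0 sets the size of the trial: "We plan to enroll a maximum of 35 patients". Section 6.2 sets it again: "We will enroll a total of 35 evaluable patients".

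Evaluable is defined twice, to much the same effect. Section 6.0: "The evaluable study population will consist of patients who reach the 6-month evaluation point for local control". Section 4.0, for the interim look: "the first 20 evaluable (defined as patients who complete the 6 month follow up) patients".

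The decision rules are absolute counts. For stage 1: "If there are at least 11 patients among the first 20 who achieve LC at 6-months, then an additional 15 patients will be enrolled". For the final analysis: "if there are at least 25 patients achieving LC at 6-months among all 35 patients, then we will reject H0".

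Only one replacement rule is given, in section 6.0: "Patients unable to complete at least 80% of their prescribed dose will be replaced". It does not cover death or loss to follow-up after a completed course. Section 6.1 takes 70 lesions from 35 treated patients, which leaves no allowance for attrition.

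**The concern.** An enrolment maximum of 35 and a requirement of 35 evaluable patients are the same number only when attrition is zero. The protocol does not expect that: section 2.0 describes these patients as often having a short life expectancy, and overall survival is a secondary endpoint.

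The interim look repeats the conflict. Section 4.0 bases it on the first 20 evaluable patients, while section 6.2 describes 20 patients being enrolled to stage 1.

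Two things depend on which figure governs. One is the maximum number of patients to be treated. The other is the final decision, because the 25-success threshold is stated only for a denominator of 35.

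**Working it through.** **Inputs from the protocol (section 6.2 and its design table).** Null LC rate 0.55; alternative 0.75; one-sided alpha 0.05; type II error 0.20; 20 patients in stage 1, continuing with 11 or more successes; 35 in total, rejecting the null with 25 or more.

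**Assumed input.** The proportion d of enrolled patients not evaluable at 6 months. The protocol gives no rate, so a range is used.

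**Step 1: reproduce the stated design.** Stage 1 stopping probability is P(Bin(20, p) ≤ 10): 0.4086 at p = 0.55 and 0.0139 at p = 0.75, matching the protocol's 0.409 and 0.014. The normal-approximation sample size is

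n = [(1.645·√(0.55·0.45) + 0.842·√(0.75·0.25)) / 0.20]² = 34.97, rounded up to 35.

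So 35 is the number of patients the test must analyse. The exact probability of rejecting is

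Σ (x = 11 to 20) P(Bin(20, p) = x) · P(Bin(15, p) ≥ 25 − x),

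which is 0.0354 at p = 0.55 and 0.758 at p = 0.75. The starting point for what follows is therefore 0.758.

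**Step 2: hard cap, threshold held at 25, a fixed number evaluable.** The first 20 evaluable patients form stage 1 and the rest form stage 2.

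| Evaluable of 35 | Observed LC needed | Chance of rejecting at true LC 75% |
|---|---|---|
| 35 | 71.4% | 0.758 |
| 34 | 73.5% | 0.664 |
| 33 | 75.8% | 0.553 |
| 32 | 78.1% | 0.432 |
| 30 | 83.3% | 0.203 |
| 28 | 89.3% | 0.055 |
| 25 | 100% | 0.0008 |
| 24 or fewer | not attainable | 0 |

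The threshold is out of reach only when 35 − 24 = 11 or more patients are not evaluable (11/35 = 31%).

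**Step 3: the same with random attrition.** The number evaluable is M ~ Bin(35, 1 − d), and the step 2 probabilities are averaged over M. The last column is 35/(1 − d), rounded up.

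| d (assumed) | Chance of rejecting at true LC 75% | P(M ≥ 25) | Enrolment needed for 35 evaluable |
|---|---|---|---|
| 0% | 0.758 | 1.000 | 35 |
| 5% | 0.575 | 1.000 | 37 |
| 10% | 0.384 | 1.000 | 39 |
| 20% | 0.112 | 0.925 | 44 |
| 30% | 0.018 | 0.510 | 50 |

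Every non-zero rate needs more than 35 enrolled.

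**Step 4: cut-offs for a smaller attained number.** These are exact binomial tails at 0.55 and 0.75; adding the stage 1 rule does not change them to three decimals.

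- 30 evaluable: at least 22 gives alpha 0.031 and power 0.67; at least 21 would give alpha 0.069.
- 25 evaluable: at least 19 gives alpha 0.026 and power 0.56; at least 18 would give alpha 0.064.

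**The case against.** The best answer is that the cap is loose wording for 35 evaluable patients. Section 6.2, which holds the operative design, says evaluable. Section 4.0 counts the first 20 evaluable patients, which implies accrual until that number is reached. Section 6.0 itself provides for replacement, so it already allows for more than 35 enrolled. On this reading attrition costs no power. This stands, and it is why the losses in steps 2 and 3 are conditional. It does not remove the conflict: the one stated maximum is then wrong, and the protocol has no real ceiling on enrolment.

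It can also be said that rules for an attained sample size belong in the statistical analysis plan, and that section 6.1 justifies the sample size by the precision of the lesion-level interval rather than by the 25-of-35 rule. Both are fair. The absence of attained-number cut-offs alone would not be a finding. But the enrolment maximum, the evaluable number and the rejection rule are all fixed in the protocol, and they disagree there.

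A reader might go further in three ways that the document does not support:

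- **That an effective regimen would usually be declared a failure because of attrition.** At 5% attrition the chance of success is still 0.575, no rate is given, and 24% of trials (1 − 0.758) miss the threshold with no attrition at all.
- **That the threshold is impossible to reach.** This needs 11 or more of 35 not evaluable. Even at 30% expected attrition the chance of having at least 25 evaluable is 0.51.
- **That the 73 patients in the supplementary baseline table show a breach of the cap.** That table reports results. It does not say how many patients were evaluable or which limit applied, so it cannot show a breach.

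**Conclusion.** The inconsistency is real and lies in a figure on which the decision rule rests. Its size depends on the reading. With a hard cap of 35 and the threshold kept at 25, power at 75% LC falls from 0.758 to between 0.575 and 0.018 over assumed attrition of 5% to 30%. With 35 read as evaluable, power stays at 0.758 and the error is confined to the stated maximum. The figures assume that attrition is unrelated to LC, that patients are independent, and that the first 20 evaluable patients form stage 1. The point should be corrected; it does not show that the trial was bound to fail.

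**What to change.** Choose one of two routes and use the same terms in sections 4.0, 6.0, 6.1 and 6.2, including for the 20 patients of stage 1.

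1. **Define 35 as evaluable.** Restate section 6.0 as 35 evaluable patients and add a separate total enrolment ceiling with the attrition assumption behind it (39, 44 or 50 enrolled at 10%, 20% or 30%). This keeps the decision rule and its power. The cost is more patients treated and followed than the present maximum allows.
2. **Keep 35 enrolled.** Add a table of cut-offs by attained evaluable number at one-sided alpha of at most 0.05, for example at least 22 of 30 or at least 19 of 25. No extra patients are needed, but power falls to 0.67 and 0.56 respectively, against the planned 0.80, and the protocol should say so.

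Counting every treated patient as evaluable would align the wording but would not restore power. If those who do not reach 6 months count as failures, the chance of at least 25 of 35 is P(Bin(35, 0.75·(1 − d)) ≥ 25), which is again 0.384, 0.112 and 0.018 at 10%, 20% and 30%.

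Either route is a change of protocol wording.

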### **Ineligibility**

Patients and/or their disease meeting any of the following criteria are ineligible for enrollment.

1. Less than 18 years old.
2. Five or more metastatic brain lesions.
3. Brain lesion(s) greater than 5 cm in diameter.
4. Lesion(s) involving the brainstem, optic chiasm or optic nerve(s).
5. Patients unable to have IV contrast for CT and MRI imaging.
6. Patient unable to have an MRI of the brain.
7. Patients willing to be treated with frame-based Gamma Knife SRS at MD Anderson main campus or MD Anderson at The Woodlands.
8. Positive pregnant status confirmed by serum or urine pregnancy test.
9. Primary small cell lung cancer, myeloma, lymphoma, leukemia, or other histologies not optimally treated with SRS.
10. Patients currently receiving chemotherapy/biologic/immunotherapy as these need to be held during FFSRT
11. Prior whole brain radiotherapy or conventional external beam radiotherapy.

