Those having access to the data include the study PI and research team personnel. Users are authenticated against MDACC's Active Directory system. External collaborators are given access to the database once approved by the PI, with their access expiring in 6 months but renewable in 6 months increments at the request of the PI. The application is accessed through Secure Socket Layer (SSL). All protected health information (PHI) will be removed from the data when it is exported from REDCap for analysis. All dates for a given patient will be shifted by a randomly generated number between 0 and 364, thus preserving the distance between dates. Dates for each patient will be shifted by a different randomly generated number. Following publication study data will be archived in REDCap. Since study data may be useful for future research studies performed under separate IRB approved protocols, study data will be archived indefinitely in REDCap. Since REDCap is a secure electronic database with controlled access, and because patient identifiers may be needed to link study data to data from other sources under future IRB approved protocols, patient identifying information will be retained in the archived database.

Initial data collection will include for each individual patient: baseline patient demographics, histology, Karnofsky performance status (6), presence or absence of systemic metastatic disease outside the brain, controlled or uncontrolled primary cancer, number of brain metastases, size and volume of largest brain metastasis treated as well as total volume of brain disease treated, dose prescribed and dose delivered to each brain lesion, and steroid use.

Patients will be followed every three months with history, clinical examination and brain MRI for 1 year. Follow up data collection at each follow-up visit will include the following:

1. Central nervous system toxicity such as Central nervous system necrosis, based on the CTCAE version 4.0.
2. Local failure in the brain on follow-up MRI defined as follows :
  - A. At least 20% increase in sum longest distance relative to lesion size prior to radiation treatment (reference 7 describes the RANO group criteria which is slightly different and uses nadir size rather than size prior to radiation)
3. Distant failure in the brain defined as additional new brain metastatic lesion(s) outside the irradiated region.
4. Overall survival.

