If new lesion(s) are identified during follow up, the patient will be considered for FFSRT on protocol at the discretion of the treating physician. These new lesions are also followed every 3 months for 1 year with MRI and are considered for local control (LC) at the 6 month time point.

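### A study lesion re-irradiated or covered by whole-brain radiotherapy before month 6, without recorded 20% growth, is scored as controlled by FFSRT, and a resected lesion has no defined class

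*Protocol*

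**What the plan says.** Section 6.0 sets the endpoint per lesion: "The primary endpoint is lesion failure within the first 6 months based on imaging assessments for each lesion". Section 6.1 likewise estimates the incidence of lesion failure by month 6. Both wordings are cumulative.

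Section 4.0 gives one criterion for local failure on follow-up MRI: "At least 20% increase in sum longest distance relative to lesion size prior to radiation treatment". New disease elsewhere is a separate item: "Distant failure in the brain defined as additional new brain metastatic lesion(s) outside the irradiated region". The list is introduced by "Follow up data collection at each follow-up visit will include the following" and names four items: CNS toxicity, local failure, distant failure and overall survival.

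On who is analysed, section 6.0 says: "The evaluable study population will consist of patients who reach the 6-month evaluation point for local control". It sets no condition on brain treatment received in the meantime.

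On further treatment, section 4.0 says: "If new lesion(s) are identified during follow up, the patient will be considered for FFSRT on protocol at the discretion of the treating physician". The Ineligibility list bars "Prior whole brain radiotherapy or conventional external beam radiotherapy" at entry. Nothing is said about these, or about surgery, after FFSRT.

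The decision rule in section 6.2 works at patient level with the local control (LC) rate at 6 months. The null is 55% or less and the alternative 75% or more. The trial continues with at least 11 of 20 controlled and rejects the null with at least 25 of 35.

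**The concern.** In a single-arm trial, 6-month control can be credited to FFSRT only if no other treatment reached the lesion first. Take a patient given whole-brain radiotherapy at month 3 for new lesions, whose study lesions had not yet grown by 20%. At month 6 those lesions are measurable, below the threshold and scored as controlled, although two treatments contributed. A lesion resected at month 4 for symptoms after 15% growth has no diameter to compare, and the protocol does not say what it counts as.

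Where such a lesion would otherwise have gone on to fail, the error runs toward success, and there is no control arm to reveal it. Section 6.2 says the results are to inform the design of a Phase III study, so an inflated rate would carry forward.

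**Working it through.** **Reading the rules together**

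| Situation before month 6 | Class under the protocol |
|---|---|
| 20% growth on MRI, then salvage | Failure under sections 6.0 and 6.1; open if section 6.2 is read as status at the visit |
| Less than 20% growth, then re-irradiated or covered by whole-brain radiotherapy | Measurable and below threshold, so controlled |
| Less than 20% growth, then resected | Undefined |
| New lesion elsewhere treated with focal FFSRT | Study lesion ordinarily untouched; no problem |

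Section 6.0 allows 3-month assessment intervals with a window of plus or minus 2 months, so treatment can precede documented growth.

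**Reproducing the plan's figures.** Inputs from section 6.2: n1 = 20, stop at 10 or fewer; n = 35, reject at 25 or more; LC 0.55 under the null and 0.75 under the alternative.

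- P(stop at stage 1) = P(X ≤ 10 | n = 20, p). This gives 0.4086 at p = 0.55 and 0.0139 at p = 0.75. The plan states 0.409 and 0.014; both reproduce.
- P(reject) = sum over x = 11 to 20 of P(X1 = x) × P(X2 ≥ 25 − x | n = 15). At p = 0.55 this gives 0.0354, within the nominal 0.05.

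**Sensitivity to masking.** The protocol gives no rate of later brain treatment, so let s be the assumed share of truly failing patients read as controlled. Observed LC is q = p + (1 − p) × s. With p = 0.55, the expected number of true failures among 35 is 0.45 × 35 = 15.75, and the mean number masked is 15.75 × s.

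| s | Mean patients masked | q | P(stop at stage 1) | P(reject) |
|---|---|---|---|---|
| 0 | 0 | 0.550 | 0.409 | 0.035 |
| 5% | 0.8 | 0.573 | 0.331 | 0.062 |
| 10% | 1.6 | 0.595 | 0.260 | 0.101 |
| 20% | 3.2 | 0.640 | 0.142 | 0.232 |

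**At the boundary.** 25/35 = 71.4% rejects the null; 24/35 = 68.6% does not. One reclassified patient can therefore decide the result.

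**At lesion level.** With the 70 lesions expected in section 6.1, each masked failure lowers the failure incidence by 1/70, or 1.4 percentage points. That is small beside the planned interval of 0.38 to 0.62. The consequence lies mainly in the patient-level rule.

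**The case against.** A reader might infer that any lesion given other brain treatment is counted as an FFSRT success. The documents do not support that. No sentence says so, and the cumulative endpoint wording means that salvage after documented 20% growth, a common reason to resect or re-irradiate, leaves the lesion a failure. Focal FFSRT to new lesions (2 mm margin, section 5.0) does not ordinarily treat the study lesion, so the provision for new lesions does not by itself show contamination. Eligibility describes lesions that are not optimal for surgery, which makes resection less typical. All of this stands.

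A reader might also infer that the bias could never be corrected. That is too strong. The follow-up list is not said to be exhaustive, each visit includes history and examination, on-protocol FFSRT is known to the study, and identifiers are retained. Later treatment could be recovered in part, but less reliably than if it were collected prospectively.

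An analysis plan that is not shown may hold a scoring rule. But the failure definition, the evaluable set and the data list are fixed in this protocol, and a later rule would depend on data that the list does not name.

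Finally, the size rests on assumption. If, for example, 10 to 20% of 35 patients (about 4 to 7) had other brain treatment and half of them would otherwise have failed, 2 to 3 failures would be masked. From 22/35, two masked failures give 24/35, which does not reject; only three reach 25/35.

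**Conclusion.** The point holds in a bounded form. A size-only criterion, applied to everyone who reaches the 6-month evaluation, credits FFSRT with control of sub-threshold lesions that were re-irradiated or covered by whole-brain radiotherapy. It leaves resected lesions unclassed. The section 6.2 wording, if read as status at the visit, would also let salvaged failures count as controlled.

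At a true LC of 55%, masking an assumed 5 to 20% of true failures raises the chance of wrongly rejecting the null from 0.035 to between 0.062 and 0.232. At the low end, fewer than one masked patient on average takes it past the nominal 0.05. How often masking would occur cannot be taken from the documents, so these figures show the rule's sensitivity and are not an estimate of the bias. The gap is worth closing because the decision can turn on one patient and the change is small.

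**What to change.** 1. Section 4.0: add to the follow-up list the date, type and target of any later brain-directed treatment.
2. Sections 6.0 and 6.2: state that patient-level LC means no failure of any study lesion at any assessment up to 6 months, so that later treatment does not reverse a failure.
3. Section 6.0: state that a study lesion resected or re-irradiated for suspected progression within 6 months counts as a local failure on that date, unless pathology shows necrosis only. State also that a lesion covered by later whole-brain or overlapping radiation is scored on the last MRI before that treatment and flagged, and that MRIs after it are not used to credit 6-month control.
4. Section 6.3: report 6-month LC with and without the affected patients. This is needed because a lesion flagged under item 3 may still be scored as controlled on its last earlier MRI.

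The cost is a few case-report fields and a few sentences. Reported LC may be slightly lower. The failure convention in item 3 is one of several that could be defended, and it should stay limited to suspected progression: at a true LC of 75%, recounting 5% of controlled patients as failures gives 0.75 × 0.95 = 0.7125 and lowers P(reject) from 0.758 to 0.575. Which later treatment a patient receives is not affected.

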## **2.0 Rationale**

Solitary and oligometastatic brain disease has been effectively managed with frame-based SRS in a single fraction with Gamma Knife, Cyber Knife or linac-based treatment delivery. (1) However, there are published data to suggest that similar local control and toxicity profiles can be achieved with FFSRT. (2,3,4,5) If, in fact, FFSRT is as effective and safe as frame-based single fraction SRS, then more patients would have access to the therapy, since 1) a neurosurgical procedure with frame would not be necessary, and 2) the equipment necessary for FFSRT is more readily available at radiation oncology facilities. In the setting of health care cost containment, if FFSRT is proven to be as effective as frame-based, single-fraction SRS, it would not be necessary to purchase the additional equipment otherwise needed for centers to offer the frame-based treatment for patients with oligometastatic brain disease. In the setting of the MD Anderson Regional Care Centers, currently only The Woodlands center offers frame-based SRS. Therefore, all patients eligible for focal treatment for their oligometastatic disease must be referred either to the Texas Medical Center or to The Woodlands facility. The additional travel, time and expense may be a burden for patients, who often have limited life expectancy.

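### Restricting the evaluable set to patients who reach 6 months drops documented early local failures from the primary estimate and from both decision rules

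*Protocol*

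**What the plan says.** Section 6.0 defines the endpoint: "The primary endpoint is lesion failure within the first 6 months based on imaging assessments for each lesion". Section 4.0 sets the imaging schedule: "Patients will be followed every three months with history, clinical examination and brain MRI for 1 year". A failure can therefore be on record well before month 6.

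The analysis set is defined by a later event. Section 6.0: "The evaluable study population will consist of patients who reach the 6-month evaluation point for local control". Section 4.0 applies the same idea to the stage 1 decision, which uses "the first 20 evaluable (defined as patients who complete the 6 month follow up) patients".

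Section 6.2 tests LC of at most 55% against at least 75% at the patient level. The trial stops if 10 or fewer of 20 patients have LC, and H0 is rejected if 25 or more of 35 do. Section 6.3 reports LC and lesion failure as proportions with exact 95% intervals and keeps Kaplan-Meier for intracranial PFS and OS.

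The number of patients is stated in ways that do not agree. Section 6.0: "We plan to enroll a maximum of 35 patients". Section 6.1 counts 35 treated patients. Section 6.2: "We will enroll a total of 35 evaluable patients".

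**The concern.** Whether a lesion failed within 6 months can be settled before month 6; whether a patient belongs to the analysis set cannot. A patient with a failure on the 3-month MRI who does not reach the 6-month evaluation has had the primary event but is not evaluable. Nothing in the protocol keeps that patient as a failure, and a simple proportion has no censoring or competing-event mechanism to recover the information. The Rationale describes these patients as ones "who often have limited life expectancy", so loss before 6 months has to be expected.

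The primary lesion failure rate, the patient-level LC rate, the futility stop and the final test all use this set, and section 6.2 intends the results to inform a Phase III design. If failed patients are lost more often than controlled ones, LC looks too good, the futility stop weakens and the one-sided 0.05 level is no longer protected.

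**Working it through.** **Inputs from the protocol.** Null LC 55%, alternative 75%, one-sided alpha 0.05; stage 1 stop at 10 or fewer of 20; rejection at 25 or more of 35 (section 6.2). **Assumed.** The proportions completing 6 months, because the protocol gives no death or dropout rate.

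**Step 1: the plan's own figures.** P(X ≤ 10 | n = 20, p) is 0.4086 at p = 0.55 and 0.0139 at p = 0.75, matching the stated 0.409 and 0.014. For the full rule,

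P(reject) = Σ over x from 11 to 20 of P(X1 = x) · P(X2 ≥ 25 − x), with X1 from 20 and X2 from 15 patients.

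This gives 0.035 at 55% and 0.758 at 75%. (The stated type II error of 0.20 implies power of 0.80; that gap is a separate matter.)

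**Step 2: dropping known failures, with no loss model.** Take an observed 25/35 = 71.4%, which rejects H0, and restore k documented failures that had been excluded:

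| k | LC with failures restored |
|---|---|
| 2 | 25/37 = 67.6% |
| 5 | 25/40 = 62.5% |
| 8 | 25/43 = 58.1% |

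**Step 3: bias against the true rate.** Let c and f be the proportions of controlled and failed patients who complete 6 months. Then

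apparent LC = LC·c / [LC·c + (1 − LC)·f].

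For example, at LC = 0.55, c = 0.9, f = 0.7: 0.495 / (0.495 + 0.315) = 0.611. With 35 evaluable patients and a true LC of 55%:

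| Completion, controlled / failed | Apparent LC | P(stop at stage 1) | P(reject H0) |
|---|---|---|---|
| Equal, e.g. 70% / 70% | 55.0% | 0.409 | 0.035 |
| 100% / 90% | 57.6% | 0.320 | 0.067 |
| 90% / 70% | 61.1% | 0.213 | 0.140 |
| 70% / 50% | 63.1% | 0.162 | 0.201 |
| Reversed, 70% / 80% | 51.7% | 0.528 | 0.014 |

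**Step 4: do simple repairs work?**

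- *Count deaths without failure as controlled and keep the cut-offs.* Assume 20% (30%) die before failure could be seen and 55% of the rest are controlled. Counted LC is 0.20 + 0.80 × 0.55 = 64% (0.30 + 0.70 × 0.55 = 68.5%), and P(reject) is 0.23 (0.43). That is as large as the problem being repaired.
- *Restore failures but still exclude controlled patients who are lost.* With 10% of controlled patients lost, a true 55% appears as 0.495 / (0.495 + 0.45) = 52.4% with P(reject) 0.017, and a true 75% as 0.675 / (0.675 + 0.25) = 73.0% with P(reject) 0.66, against 0.035 and 0.76 without loss. The rule becomes conservative.

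**The case against.** The best counter-argument is that the direction of bias is not established. Equal loss leaves LC at 55%, and heavier loss of controlled patients lowers it. That stands: upward bias is plausible, because local failure may precede death or withdrawal, but the protocol does not say so. It does not rescue the definition, which discards observed events whichever way the net bias runs.

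The affected group is also narrower than it first seems. Section 6.0 allows visits within 2 months either side of the 3-month schedule, so a patient who dies at month 5 may already have had the 6-month evaluation. Failure does not end follow-up either. Only patients who fail and are then lost before that evaluation drop out.

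A reader might infer four further things that the documents do not support:

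- *That 6-month OS is 100% by construction.* Section 6.0 ties the evaluable set to local control. Section 6.3 analyses OS and intracranial PFS by Kaplan-Meier, with death as an event for the latter, and restricts neither to completers.
- *That the 73 patients in the supplementary baseline table reveal the planned or evaluable fraction.* The table describes reported patients. It is not a planning figure, and nothing says that 35 of them were evaluable.
- *That replacing patients on dose is part of the same problem.* The rule "Patients unable to complete at least 80% of their prescribed dose will be replaced" concerns courses of 3 or 5 fractions, over before any follow-up MRI. It is a separate matter.
- *That H0 could become impossible to reject as well as too easy to reject.* The first needs a hard cap of 35 enrolled with fewer than 25 completing; the error rates in step 3 need 35 evaluable. Both cannot hold, so the conflicting numbers are wording to reconcile and not a second harm to add.

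**Conclusion.** Wrong as written. The evaluable set contradicts the endpoint: an event that counts within 6 months is discarded if the patient does not reach the 6-month evaluation. This is a stated rule, not detail left to an SAP.

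It is certain that excluding a documented failure raises LC compared with counting it. It is not certain that LC is inflated against the true rate; that requires failed patients to be lost more often than controlled ones. Over the assumed completion rates, P(reject H0) at a true LC of 55% runs from 0.014 to 0.201 against 0.035 with equal loss, and a 10-point deficit among failed patients alone (100% / 90%) already takes it to 0.067, above the stated 0.05. Severity: should fix.

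**What to change.** 1. State in sections 4.0, 6.0 and 6.2 that any local failure documented by 6 months counts as a failure in every LC analysis and in both decision rules, whatever the later follow-up.
2. Estimate 6-month lesion failure from all patients who start FFSRT by cumulative incidence, with death without local failure as a competing event and loss to follow-up censored. Show the rate among 6-month completers as a sensitivity analysis.
3. Fix in advance how patients who die or are lost without failure enter the 11/20 and 25/35 counts. Do not simply count them as controlled under the present cut-offs (step 4). Report LC with them counted as controlled, as not controlled, and excluded.
4. Reconcile the maximum of 35 enrolled (section 6.0) and the 35 treated (section 6.1) with the 35 evaluable (section 6.2).

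**Cost.** Wording changes and modest additional analysis. The LC rate may look less favourable. If patients lost without failure stay out of the counts, power falls: to 0.66 from 0.76 at a true LC of 75% if 10% of controlled patients are lost. Whether accrual changes depends on how item 4 is settled.
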